# A tailored Internet-delivered modular intervention based on cognitive behavioral therapy for depressed older adults: a study protocol for a randomized controlled trial

**DOI:** 10.1186/s13063-021-05903-4

**Published:** 2021-12-16

**Keywords:** Depression, Elderly, CBT, ICBT, RCT, Internet-based intervention

## Abstract

**Background:**

Depression is most common among the elderly and is associated with major impairment. With limited accessible treatments available, remotely provided interventions are needed. Internet-based interventions have been proven effective for a number of mental and somatic health problems. However, the elderly population has received relatively limited attention in previous studies. This study aims to address this gap by investigating the effectiveness of a tailored Internet-delivered modular intervention based on cognitive behavioral therapy (CBT).

**Methods:**

A minimum of 60 participants will be recruited and randomly assigned to groups in a two-armed parallel controlled trial with a waiting list. The intervention group will have access to an 8-week therapist-supported modular intervention. The waiting list group will be instructed to wait for 8 weeks and then granted access to the intervention for 8 weeks. Pre, post, and 3-, 12-, and 24-month follow-up assessments are planned for measuring changes in depression symptoms, anxiety symptoms, and psychological well-being using PHQ-9, GDS, GAD-7, and WHO-5. Primary outcomes of all the participants will be analyzed using the intention-to-treat principle, and within- and between-group effect sizes will be calculated.

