### Sample size {14}

A power calculation was conducted using GLIMMPLSE software, which is helpful for sample-size calculation for repeated measures and longitudinal studies [33]. Statistical power was set to 0.8, including pre- and post-treatment repeated measurement points; an *α* was set at 0.05. A total sample of 70 participants was needed to reach 80% power. Factoring in an estimated dropout rate of 10% we seek to randomize 78 participants (39 participants in each group). The power analysis is based on the primary outcome variable’s Patient Health Questionnaire (PHQ-9) [29] means and standard deviations of the two time points data based on the results from a similar unpublished study from Sweden (intervention group pre-treatment (T1) *M* = 12.45, *SD* = 4.38, post-treatment (T2) *M* = 6.57, *SD* = 4.34, control group T1 *M* = 14.22, *SD* = 4.19, T2 *M* = 8.11 *SD* = 4.92), with a 1:1 allocation ratio.

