### Recruitment {15}

Participants will be recruited through social media outlets, a press release and advertisement in local papers, interviews on radio, and local television. In order to obtain a needed sample size, recruitment period might be prolonged and paid advertisement in social media targeting older adults might be intensified.

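### The abstract's minimum of 60 randomised participants is underived and lies below the 70 needed and 78 to be randomised in the sample-size section

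*Protocol article*

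**What the plan says.** The article gives three sample sizes in two places.

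- **Abstract, Methods:** "A minimum of 60 participants will be recruited and randomly assigned to groups".
- **Sample size {14}:** "A total sample of 70 participants was needed to reach 80% power", and then "Factoring in an estimated dropout rate of 10% we seek to randomize 78 participants (39 participants in each group").

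Recruitment {15} adds "In order to obtain a needed sample size, recruitment period might be prolonged" and attaches no number. The 60 appears only in the abstract. No section derives it, justifies it or describes it as a feasibility limit.

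**The concern.** The 60 and the 78 count the same thing, participants randomised, and they differ. The lower figure is also below the 70 that the plan says it needs before any allowance for dropout. A reader of the abstract alone would take 60 as the planned size. A later report could compare achieved enrolment with either number, and a trial that enrolled between 60 and 77 could be described as having met its plan or as having missed it.

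**Working it through.** **Inputs.** From Sample size {14}: "Statistical power was set to 0.8"; alpha "was set at 0.05"; 70 needed; 10% dropout; 78 randomised; 1:1 allocation. From the abstract: 60. The article does not say whether alpha is one- or two-sided, so two-sided is assumed and one-sided is shown as a check.

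**Step 1: the plan's own dropout step.** 70 / (1 − 0.10) = 77.8, rounded up to 78. This reproduces, and 78 × 0.9 = 70.2. So 70 and 78 agree with each other, and 60 is the odd figure out.

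**Step 2: the gap.**
- 70 − 60 = 10 below the stated need with no dropout at all.
- 78 − 60 = 18 below the randomisation target; 18 / 78 = 23%.

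**Step 3: relative loss of power, taking 80% at 70 as given.** The plan states no standardised effect, so one is back-solved.
- Normal approximation: d = (1.960 + 0.842) × √(2/35) = 0.670.
- At 30 per group: power = Φ(0.670 × √(30/2) − 1.960) = Φ(0.634) = 73.7%.
- At 39 per group: Φ(0.670 × √(39/2) − 1.960) = Φ(0.997) = 84.1%.
- With the t distribution: d = 0.679, and power is 73.5% at 60 and 84.2% at 78.
- One-sided alpha of 0.05, calibrated the same way: 74.3% at 60.

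**Step 4: does 70 follow from the printed PHQ-9 values?** The calculation is described as "including pre- and post-treatment repeated measurement points". The pre-post correlation r is not given, so values from 0 to 0.9 were tried.
- Post-treatment difference: 8.11 − 6.57 = 1.54. Pooled SD = √((4.34² + 4.92²)/2) = 4.64, so d = 0.33. This needs 2 × (1.960 + 0.842)² × (4.64/1.54)² ≈ 143 per arm, 286 in total (226 one-sided).
- Difference in change: intervention 12.45 − 6.57 = 5.88; control 14.22 − 8.11 = 6.11. The gap is 0.23 in favour of control and would need more than 1,000 per arm at every r tried.
- Average of the two time points: difference 1.655; 116 to 218 in total.
- Baseline-adjusted analysis that keeps the full 1.54: 70 is reached only at r of about 0.87. Adjusting for the printed baseline gap leaves a difference of 0.01 at r = 0.8 and −0.18 at r = 0.9.

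None of these readings supports 70. On the printed post-treatment difference, t-test power is about 24% at 60, 28% at 70 and 30% at 78. The percentages in step 3 therefore compare sizes on the plan's own claim; they do not estimate the trial's power.

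**The case against.** The best defence is that a minimum and a target are different things. At least 60 and a goal of 78 can both be true, and no section says that recruitment stops at 60. This stands. A reader might infer that the abstract permits closing at 60, but the article contains no such rule. Recruitment {15} speaks of prolonging recruitment until the required number is reached, and the only section that names a required number is Sample size {14}. The natural reading is that recruitment is extended towards that section's figures, not towards 60.

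A reader might also apply the 10% dropout to 60, obtain 54, and quote about 69% power. That does not describe the main analysis. Section {20c} fills missing values by carrying the last value forward, and section {18a} collects baseline data before randomisation, so dropouts stay in the intention-to-treat set and 60 randomised means 60 analysed. The 54 would fit a completer analysis, which the plan makes secondary.

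Two further points limit the practical effect. Trial design {8} calls the trial exploratory. Trial status gives recruitment as planned to May 2021, whereas the article is dated December 2021, so on that schedule correcting the abstract would not change when recruitment closed.

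What the defence does not answer is why a stated minimum lies below the number that the same article says is needed. A floor of 70 or more would fit the sample-size section; an unlabelled 60 does not.

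**Conclusion.** The point holds as an inconsistency between the abstract and the body. The abstract's 60 is underived and unlabelled, 10 below the stated need and 18 (23%) below the randomisation target. This rests on the printed figures alone. The dropout arithmetic in the sample-size section is correct.

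A trial that met only the abstract's minimum would fall short of the stated 80%. The size of the shortfall, about 6 to 7 percentage points (80% to 73–74%), assumes that 80% at 70 is right, that the test is a two-sided two-group comparison, that all 60 are in the intention-to-treat set, and that carried-forward values do not dilute the effect. It is an illustration of relative loss.

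It would also be wrong to conclude that moving the abstract to 78 secures 80% power. The 70 does not reproduce from the printed means and SDs. That is a separate and larger problem, which this correction does not cure.

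**What to change.** Replace the abstract's figure with the randomisation target in Sample size {14}, 78 participants with 39 per group, and name the same number in Recruitment {15} as the size that recruitment may be prolonged to reach. If 60 was meant as a feasibility floor, say so and state that it does not deliver the power given in the sample-size section. Do not print a power figure for 60: 73 to 74% would rest on a calculation that the printed PHQ-9 values do not support.

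The cost is one sentence in the abstract and a few words in Recruitment {15}; the target of 78 is already in the plan. If the sample-size calculation is redone, the abstract and the recruitment section should both carry the recalculated number.

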**Discussion:**

Internet-based interventions could help address the existing treatment gap for depressed older adults. However, to date, the effectiveness of Internet-based CBT (ICBT) for depressed older adults has only been tested in a few studies. This trial will demonstrate if Internet-based CBT is effective for this population when compared to a waiting list control. Further analysis of secondary outcomes and participant behavior in the intervention will potentially reveal effectiveness moderating factors.

**Trial registration:**

ClinicalTrials.gov NCT04728204. Registered on 15 January 2021. https://www.clinicaltrials.gov/ct2/show/NCT04728204?term=NCT04728204&draw=2&rank=1

## Administrative information

Note: the numbers in curly brackets in this protocol refer to SPIRIT checklist item numbers. The order of the items has been modified to group similar items (see http://www.equator-network.org/reporting-guidelines/spirit-2013-statement-defining-standard-protocol-items-for-clinical-trials/).

## Background

Depression is one of the most prevalent mental health disorders among the elderly [1, 2] and has been reported as one of the three largest contributors to the global burden of disease [3]. Studies have shown that depression can affect up to 8.1 % (major depressive disorder, MDD) and 14.1% and 24% (mild and sub-clinical depression) of the population [4]. Among individuals aged 65 to 100 years, 2.7% of men and 4.4% of women have major depression [5]. Lifetime prevalence of depression decreases with age and is estimated to be 9.6% for men and 20.4% for women [5]. Age itself has been demonstrated to have little to no effect on depression risk when controlling for income, physical disability, and social support [6]. Late-life depression has also been associated with cognitive dysfunction, disability, medical illnesses, and social isolation [7]. Finally, untreated depression can have serious implications on the quality and quantity of life [8].

Effective and accessible treatments are needed for treating depression in the elderly. A meta-analysis revealed that treating depressed older adults with antidepressants had unsatisfactory results and frequently led to adverse events [9]. Effective psychological treatments are therefore needed. A recent meta-analysis by Cuijpers and colleagues demonstrated that CBT and supportive counseling were effective for treating depression even after addressing biases [10]. However, because of barriers such as stigma, lack of providers and treatments, patient somatization, and denial, many cases of depression are not recognized and treated [11]. The global COVID-19 pandemic has limited the accessibility of face-to-face mental health services even further because older individuals are considered to be at higher risk and advised to limit their movement. Internet-based interventions have been developed and tested in controlled trials. These interventions could help fill this gap. Internet-based cognitive behavioral interventions have been found to be effective for a variety of mental and somatic health problems including depression when compared to their face-to-face equivalents [12, 13]. Most commonly depressed adult and to some extent adolescent populations have been the focus of previous research [14, 15]. To the best of our knowledge, only a few Internet-based CBT interventions for depressed older adults have been tested, but the ones that were tested report promising outcomes [16–18]. However, participant age was varied, with one trial including subjects as young as 50 years old [18]. Nevertheless, evidence on the long-term effects of such interventions is sparse and studies with longer follow-up periods [19] and older populations are needed.

Effectiveness is not the only concern with Internet-based CBT interventions. Providing treatment over the Internet poses dropout, recruitment and treatment tailoring challenges. Many previous Internet-delivered unguided treatments for depression and anxiety suffered from high dropout rates and adherence problems [20–22]. Existing evidence suggests that at least minimal therapist support improve adherence and treatment outcomes [23, 24]. In depression trials specifically, therapist assistance was associated with better outcomes and greater retention [25, 26]. Although therapeutic alliance seems to be high and somewhat similar to that documented in face-to-face treatments, it appears to have little relation to treatment outcomes [27]. Therapist guidance coupled with modular design allow for some level of individual tailoring and help avoid the one size fits all pitfall.

## Objectives {7}

The aim of this study is to test the effectiveness of an Internet-based cognitive behavioral therapy with minimal therapist support for depressed older adults. Our hypothesis is that the treatment group will have significantly larger reductions in symptoms of depression when compared to the waiting list control group post-treatment and will retain these effects at the 3-month follow-up. We will further seek to evaluate retention at 12- and 24-month follow-ups.

## Trial design {8}

This study is a parallel group, two-arm, exploratory trial with a 1:1 allocation ratio and no stratification.

## Methods

### Study setting {9}

This study will be managed from Vilnius University (Lithuania) and run in close collaboration with Linköping University (Sweden). The study will employ a secure and flexible platform developed and maintained by Linköping University [28]. Participants from all over Lithuania will be able to register as participants online. This will potentially provide an advantage in reaching a diverse demographic. The study will be conducted on a dedicated website.

### Eligibility criteria {10}

Inclusion criteria: Participants eligible for the trial must comply with all of the following at randomization: (1) 60+ years, (2) depressive symptoms, (3) access to a computer/tablet/smartphone and to the Internet, and (4) good knowledge of the Lithuanian language (reading, speaking, and writing without an interpreter). Exclusion criteria: (1) problematic alcohol use, (2) presently in any other psychological treatment, (3) severe depression, (4) suicidal ideation, and (5) significant change in psychiatric medication (during last 6 weeks).

### Who will take informed consent? {26a}

Individuals interested in participating in the study will have to visit the study website where they will receive information about the study. After familiarizing themselves with aims of the study and inclusion/exclusion criteria, they will then be redirected to a sub-site of the main website where they will be asked to read the informed consent form and to provide informed consent by selecting an option on the study website before any study procedures occur. The informed consent form is in Lithuanian language and describes the aims and procedures of the study in detail, the rights of the participants to withdraw the consent at any time and instructions to contact study team members in case of any study related adverse events during the trial. The consent form also provides contact details of the principle investigator for any study-related questions.

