#### Criteria for discontinuing or modifying allocated interventions {11b}

Participants will be instructed to contact the research team personnel if their condition deteriorates. Such a participant will be contacted within 24 h, and a thorough clinical interview will be administered via telephone by an experienced clinical psychologist. Based on the outcome of the interview, the participant might then be referred to a hospital or other appropriate services.

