### Composition of the data monitoring committee, its role, and reporting structure {21a}

A data monitoring committee is not necessary because all participants will be self-referred, all data will be coded directly to the system where no adjustments can be made to data, and all actions are logged. Furthermore, participants will have weekly contact with research team members who will monitor for any adverse events and report them to principle investigator. Participants who experience adverse events will be interviewed by a study team member with experience in clinical assessment and will be informed about available community services appropriate for their condition.

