### Adverse event reporting and harms {22}

During the trial, enrolled participants will be informed to report adverse effects to the trial administrator. An experienced clinician from the research team will contact any such participants and conduct a thorough investigation. Additionally, although adverse events in interventions are rare, post-treatment assessment will be conducted as has been recommended by Rozental and colleagues [34]. All participants initially in the intervention group and, after receiving treatment, the waiting list group will be asked to complete the Negative Effects Questionnaire (NEQ) to record any negative trial effects. All gathered data on harms will be published together with main outcome results.

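### Participants are asked to report study-related events while staff are to monitor any event, so events other than deterioration may go unreported in the waiting period and follow-up

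*Protocol article*

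**What the plan says.** Several sections of the protocol article describe how harms come to light.

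- *Who will take informed consent? {26a}*: the consent form contains "instructions to contact study team members in case of any study related adverse events during the trial".
- *Adverse event reporting and harms {22}*: "enrolled participants will be informed to report adverse effects to the trial administrator". A clinician from the team then contacts and investigates those who report.
- *Criteria for discontinuing or modifying allocated interventions {11b}*: "Participants will be instructed to contact the research team personnel if their condition deteriorates". Contact within 24 h and a telephone interview follow.
- *Composition of the data monitoring committee {21a}*: participants will have "weekly contact with research team members who will monitor for any adverse events and report them to principle investigator", and "Participants who experience adverse events will be interviewed by a study team member with experience in clinical assessment". This is part of the reason given for having no such committee.
- The harms section adds a questionnaire: "All participants initially in the intervention group and, after receiving treatment, the waiting list group will be asked to complete the Negative Effects Questionnaire". It also promises that "All gathered data on harms will be published together with main outcome results".

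Under *Who will be blinded {17a}*, neither participants nor the study team are blinded after assignment; only the data analysts are.

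**The concern.** Whether an event is study related is a causality judgement. In harms collection it is normally made after the event has been recorded, by someone clinically qualified. Here the consent-form summary puts it in the instruction to the participant. The harms section's wording (effects, not events) leans the same way, though less explicitly. The staff duty carries no such condition.

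Two things are at stake. The first is safety: on the self-report routes, the clinician hears of an event only if the participant raises it. The second is comparability. During the first 8 weeks the waiting list receives no intervention, so its members may have less reason to connect an event with the study than people working through modules with a therapist. If reporting depends on that connection, the harms published with the main results could differ between arms for reasons unrelated to how often events occurred.

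**Working it through.** The plan states no event rate or expected number of reports, so there is no figure to reproduce. The check is to set the routes side by side and ask which of them work without the participant's view of cause, in which arm, and when.

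| Route | Started by | Depends on participant's view of cause? | Intervention arm, weeks 1–8 | Waiting list, weeks 1–8 | Follow-up (3, 12, 24 months) |
|---|---|---|---|---|---|
| Consent form {26a} | Participant | Yes, as summarised | Applies | Applies | Applies if still during the trial |
| Report of adverse effects {22} | Participant | Arguably; no explicit qualifier | Applies | Applies | Applies if still during the trial |
| Deterioration {11b} | Participant | No, but covers worsening only | Applies | Applies | Not stated |
| Weekly staff contact {21a} | Staff | No | Described concretely in {11a} | Claimed in general terms only | Not described |
| Negative Effects Questionnaire {22}, Table 1 | Questionnaire | Solicited | At post-treatment | Not until after own treatment | Not scheduled |

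Reading across:

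1. **Worsening of the participant's condition.** The instruction in {11b} sets no condition about cause and excludes neither arm. Table 1 also schedules PHQ-9 and GDS at post-treatment and at each follow-up. For this kind of harm the relatedness wording does little damage.

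2. **Other events, intervention arm, weeks 1–8.** *Intervention description {11a}* has therapists giving feedback and prescribing modules weekly, so the monitoring promised in {21a} has an occasion on which to happen. The questionnaire follows at the end. The filter is largely bypassed.

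3. **Other events, waiting list, weeks 1–8.** Section {21a} speaks of participants without limiting the arm, but {11a} says only that this group waits 8 weeks. Table 1 lists weekly treatment and engagement entries and no weekly adverse-event check. The questionnaire comes only after this group's own treatment, so it gives no concurrent control data. What remains is mainly self-report under {26a} and {22}, where the wording about cause has most influence.

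4. **Other events, follow-up.** No weekly contact is described once treatment ends, and Table 1 marks the questionnaire at post-treatment only. Self-report is again the main described route. By then both groups have been offered the intervention, so the loss is chiefly one of completeness.

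The between-arm question therefore belongs mainly to the first 8 weeks, the only period with an untreated comparison group.

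**The case against.** The strongest reply is that the article only summarises, in one English clause, a Lithuanian form that is not shown. It does not say that other events should be withheld. Staff duties and participant instructions are different things, so a broader staff duty complements a narrower instruction rather than contradicting it. Section {22} uses several terms for harm loosely, and reading a strict causality test into one of them asks too much of condensed prose. Study related is also wider than treatment related: someone who worsens while waiting could well see that as study related. Finally, {11b} and {21a} open routes to a clinician that need no attribution.

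Much of this stands. A reader might infer that participants are told to report study-related events and nothing else, or that events they think unrelated can never reach a clinician. The documents support neither reading: no such restriction is written, and {11b} and {21a} provide other routes.

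A reader might also try to put numbers on an imbalance. Suppose 10% of 39 per arm have an event (39 × 0.10 = 3.9), and 50–75% of treated but 0–25% of waiting participants report it. That gives about 2–3 reports against 0–1. All these rates are assumed, and the sum treats self-report as the only route, so it merely restates its inputs.

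What the reply does not remove is the gap in periods and arms where the alternative routes are not concretely described. Section {11b} does not clearly cover an event that is not a worsening of the participant's condition. The monitoring in {21a} needs a contact at which to occur, and none is described for the waiting list or for follow-up.

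**Conclusion.** The concern holds in a limited form. The instructions to participants are narrower than the monitoring the article claims, and they ask unblinded participants to judge cause first. For deterioration, and for the intervention arm during treatment, other routes largely compensate. For other events in the waiting period and in follow-up, capture may rest mainly on self-report, so events not attributed to the study may be missed, possibly unequally by arm in the first 8 weeks.

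The size cannot be estimated from the documents. The conclusion assumes that the consent form reads as summarised and that weekly contact is not in practice extended to the waiting list. If staff do contact that arm weekly and ask about any event, the between-arm part of the concern largely disappears and only the wording needs correcting. The primary and secondary efficacy analyses and the sample size are untouched. The change is worth making because the article relies on this monitoring in place of a data monitoring committee and promises to publish the harms data.

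**What to change.** Reconcile sections {26a}, {11b}, {21a} and {22} to a single scope. Both arms should be asked, in identical words, to report any adverse event or worsening whether or not they think the study caused it. The research-team clinician already named in {22} should record relatedness after the event is logged, and events should be reported by arm. Section {21a} should also say whether weekly contact includes the waiting list.

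The cost is small: a line in the consent form, matching wording in the protocol, and the ethics approval and register update already provided for in {25}. The downside is that some unrelated events will be recorded and have to be read.

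Timing limits the gain. Recruitment began on 28 January 2021 and was planned to run to May 2021. If it closed then, the last 8-week wait would have ended around late July 2021, before the article appeared in December 2021. For participants already enrolled, the new wording would help mainly in the remaining follow-up. The results report should then state by which route events were collected in each arm and period, so that readers do not take a difference in reporting for a difference in harm.
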